## Abstract

**Background:**

Mid to late adolescence is characterised by a vulnerability to problematic substance use since the consumption of alcohol and illicit drugs is frequently initiated and increased in this life period. While the detrimental long- and short-term effects of problematic consumption patterns in adolescence pose a major public health concern, current prevention programs targeting alcohol- and other substance-using adolescents are scarce. The study described in this protocol will test the effectiveness of a web-based brief intervention aimed at reducing problematic alcohol use and promoting abstinence from illegal drugs in adolescents with risky substance use aged 16 to 18 years old in four EU-countries.

**Methods/design:**

To determine the effectiveness of our web-BI, we apply a two-arm randomized controlled trial (RCT) study design, with baseline assessment at study entry and a three month follow-up assessment. Adolescents aged 16 to 18 years from Belgium, the Czech Republic, Germany, and Sweden will be randomly assigned to either the fully electronically delivered brief intervention group (*N* = 400) or an assessment only control group (*N* = 400) depending on their screening for risky substance use (using the CRAFFT). Recruitment, informed consent, randomization, intervention and follow-up will be implemented online. Primary outcomes are reductions in frequency and quantity of use of alcohol and drugs other than alcohol over a 30 day period, as well as consumption per typical occasion. Secondary outcomes concern changes in substance use related cognitions including the constructs of the Theory of Planned Behaviour, implementation intentions, and stages of change. Moreover the study addresses a number of moderator variables, including age of first use, general psychopathology and quality of parent–child relationship.

**Discussion:**

The trial is expected to contribute to the growing literature on theory- and web-based brief interventions for adolescents. We will explore the potential of using web-based technologies as means of delivering preventive interventions. In doing so we are among the first to target the relevant group of young poly-drug users in Europe.

**Trial registration:**

Current Controlled Trials ISRCTN95538913

## Background

Mid to late adolescence constitutes a phase of major developmental changes and age-specific demands associated with the biographic transition into a more adult role [1-3]. While the hallmarks of adolescence are exploration of identity and future prospects [4,5], this phase in the lifespan is also characterized by a certain vulnerability to substance consumption [6] since the consumption of alcohol and illicit drugs is frequently initiated and increased in this life period [7,8].

The European School Survey Project on Alcohol and Other Drugs (ESPAD) periodically reports prevalence rates among students in 35 European countries. Overall, this report demonstrates a considerably high proportion of substance using adolescents particularly concerning early and heavy drinking. In 2007, an average of 90% of the 15–16 year old students in Europe had consumed alcohol at some point in their life. Most of them started to drink alcohol at the age of 13 years [9]. An average of 50% of European students experienced alcohol-intoxication at least once in their lifetime and 39% did so during the last month. Moreover, one of three European students had smoked cigarettes during the past 30 days and one of five had used cannabis at least once in his or her life, which was also true for 7% of the students regarding illicit drugs other than cannabis. Apparently substance use is rarely restricted to the consumption of a single substance as illicit drug consumption is most typically accompanied by alcohol [9]. Such poly-drug patterns appear prevalent among youth in modern Europe as emphasized in the 2009 Annual report by the European Monitoring Centre for Drugs and Drug Addiction [10].

Consumption of various substances (and their combinations) in adolescence is associated with severe adverse effects on psychological and physiological development [11,12]. Untimely (i.e., early) and hazardous use of alcohol, cannabis and other substances in early years puts youth at risk for developing chronic problematic consumption patterns that can significantly influence their developmental trajectories during the transition from child- to adulthood [13,14]. Detrimental long term effects of establishing chronic problematic consumption patterns and substance use disorders (SUDs) and the associated health problems are apparent [15]. Also, there are serious short-term consequences related to substance consumption such as accidents, vandalism, risky sexual behaviour [7], delinquency, truancy, problems of academic adjustment [12] and problems with the police or legal authorities [16]. Beyond the immense personal risks involved, problematic substance use also imposes significant economic burdens on the European Union in terms of health care costs, which translate into an estimated amount of 20 billion Euro per year caused by alcohol use in Germany alone [17]. In light of these negative consequences substance use can be qualified as a large risk potential and mayor public health concern in Western societies [18,19].

The high prevalence of substance use in Europe is a problem that has been recognized in the EU Drug Strategy 2005–2012 [20]. To date, however, in Germany as in the European Union, current prevention programs targeting alcohol- and other drug-using adolescents (i.e., early indicated prevention) that meet scientific evaluation criteria are scarce. The study described in this protocol aims at filling this gap and will test the effectiveness of a web-based brief intervention aimed at reducing alcohol use and promoting abstinence from illegal drugs among adolescents with risky substance use aged 16 to 18 years.


Although apparently more studies are required since health-related behaviour change using the internet in general is still in the early stages of development [39], recent experimental and systematic reviews suggest that brief interventions delivered entirely via computer programs [40,41] or the internet [42-44] match the efficacy of person-delivered interventions [45]. At the same time they offer a number of advantages over conventional methods. Specifically, they are easily implemented and disseminated, and they provide the opportunity to reach a large audience by improved access to interventions in a very cost effective manner [46,47]. In addition, they maintain participants’ privacy and anonymity [28], and provide flexible access at any time and location, the latter of which is especially relevant for areas lacking service possibilities. Furthermore, web-based approaches appear particularly suitable to a younger target group for which internet use is very common [48]. Nowadays, adolescents prefer the internet as means of finding information about drugs [49], and might be more willing to disclose alcohol- and drug-related behaviour in a web-delivered format because it is less stigmatising [50] and requires less problem awareness in order to be accepted [51]. This latter aspect is especially relevant for younger people, among whom denial of mental health problems is common [52].

Given these benefits, it is not surprising that computerised intervention approaches regarding substance use figure prominently in current literature [42,50]. However as Copeland and Martin [29] note, overall this literature is largely descriptive and lacks controlled trials, in particular with respect to adolescent populations. Moreover to date the literature has not adequately addressed possible mechanisms of change inherent to MI-approaches using theoretically derived constructs [53,54] and lacks a more fine-graded description of specific subgroups that benefit from such an approach (i.e., moderators).

#### Aim

Considering the promising results and the apparent benefits of electronically delivered screening and brief intervention for people with hazardous substance consumption, together with the need to investigate new ways of approaching the important target group of poly-drug using adolescents in Europe, this study primarily aims at creating a fully automatised web-based brief intervention for substance-using adolescents in four European countries and examine its effectiveness across a range of outcome measures. Secondary research questions concern potential predictors, mediators and moderators of positive outcomes.

## Method/design

The relevant target group for this study are adolescents aged 16 to 18 years from Belgium, the Czech Republic, Germany, and Sweden. To determine the effectiveness of the web-BI, we apply a two-arm RCT study design, with baseline assessment at study entry and a three month follow-up assessment. Figure 1 displays the trial design.

**Figures 1 F1:**
[figure not shown]
Study design.

### Recruitment

In contrast to other studies that test web-based interventions offline before putting them on the internet [28,55] we will launch Czech, German, Flamish, and Swedish versions of our website and motivate potential participants to visit by running online (using social networks and banner advertisements) and offline marketing campaigns. Similar to others [28] we will rely on a convenience sample from the general population. To attract adolescents, motivate them to participate and keep their attention, our intervention will be constructed to be personalised, playful and interactive, featuring an attractive graphical design and a presentation mode that factors in age-specific and gender-sensitive aspects. The aim is to generate a highly dynamic intervention that contrasts to other more informational and static web-portals. Additionally, to enhance follow-up rates, a sweepstake for participants successfully completing follow-up assessment is provided in each country.

### Study flow

The landing page will provide five language flags (languages of the four participating countries plus an English Version) for choosing a different language than the language pre-defined by browser options. Those first visiting the page will be asked for registration which requires a user name, e-mail address and a pass word. After registration respondents will be presented with a developmentally appropriate screening tool for adolescents to examine if they fulfil the inclusion criterion of a substance problem. For screening we rely on an adapted version of the CRAFFT^a ^[56] for use of alcohol and drugs. This tool uses six items and has proven criterion validity and appropriateness for identifying substance-related problems among adolescents [57] compared to other screening tools [58]. A CRAFFT score higher than 1 (i.e., at least two questions are answered with yes) demonstrates sensitivity to identify substance problems [58] and is deemed sufficient to be eligible for participating in the study. Besides a positive screen for substance-related problems, participants must be between 16 and 18 years of age. Participants matching the inclusion criteria will then receive study information including confidentiality advice,^b^ the indication of voluntariness of participation, and of human subject protections [28]. They are then asked to electronically give informed consent. Approval for the design and data collection was already obtained from the responsible authorities in each participating country, which are the Ethical Committee of the Chamber of Physicians Hamburg (Germany), Prague Psychiatric Centre (Czech Republic), University Hospital of Antwerp and the University of Antwerp (Belgium), and the Regional Ethics Board in Stockholm (Sweden).

### Assessment

Those eligible and willing to participate in the study will receive comprehensive baseline assessment questionnaires containing socio-demographic characteristics, such as age, gender, educational/vocational information, as well as their weight which will be the base for an individualised and personalised feedback in the later intervention (weight is necessary to calculate Blood-alcohol-concentration). Items concerning current substance consumption (primary outcomes) and cognitive items concerning substance use (secondary outcomes) will be assessed at baseline and follow-up. A number of potential moderator variables are included in the baseline assessment to allow for subgroup analyses. All measures are based on established scales or self-constructed according to the literature (see *Instruments* section). All assessment material will be pilot-tested for appropriateness and duration as completing the survey should not take long in order to avoid attrition.^c^

### Randomisation

Randomisation will take place after completion of the screening procedure, informed consent statement and baseline questionnaires. Random allocation to either the intervention or the control group (assessment only) will be generated automatically by an online computer program and cannot be influenced by researchers. No stratification procedure is included since the expected number of participants is sufficient to make a balanced distribution among the two parallel groups likely [59]. Randomisation checks will be conducted on baseline behavioural and psychological measures using multivariate analyses of variance (MANOVA) with consumption and consumption-related cognitions as dependent variables and intervention condition (brief intervention vs. control) as the independent variables [60]. Participants will be informed of their allocation with those in the intervention condition receiving a log-in code if they wish to exit and re-enter at a later point in time.

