### Statistical analyses

To test the efficacy of WISEteens we address the primary research question whether participation in the intervention leads to a decrease in drinking and / or drug consumption other than alcohol at follow-up after three months compared to those adolescents in the assessment-only control group. The main analysis will follow separate analyses for alcohol and drugs. For alcohol consumption we will run multivariate analyses of covariance (MANCOVA) with intervention condition as the independent variable (intervention vs. control group) on the primary dependent variables frequency and quantity (i.e., number of drinks per typical drinking occasion) of alcohol consumption, frequency of binge drinking (AUDIT-C), reductions in weekly drinking and peak drinking. Baseline alcohol units of these variables and change scores (baseline-follow-up) of motivational (i.e., implementation intentions) and the socio-cognitive constructs (i.e., intentions, attitudes, subjective norms, PBC) based on Ajzen’s Theory of Planned Behaviour (TPB) [84] will be included as covariates. For drug use other than alcohol we will analogously run separate analyses of variance (MANCOVAs) on the primary dependent variables frequency and quantity of drug use (DUDIT-C). In addition, we will test whether socio-demographic variables (age, sex, social class), country of residence (Sweden, Germany, Belgium, Czech Republic), general psychopathology, parent–child relationship, age of first use, and stage of motivation to change moderate the outcomes. Moreover we will explore possible mediated effects of our intervention on the various behavioural measures relying on multiple mediation analysis using the syntax of Preacher and Hayes [96] for SPSS, and test direct and indirect effects in a path model using AMOS 18 [97]. Path Analysis is a multivariate technique specifying relationships between observed variables akin to running several regression equations with the advantage that it allows simultaneous testing of several propositions regarding how constructs are theoretically linked and the directionality of significant relationships within one single model [98].

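### The main MANCOVA pools four countries and both sexes with no term for either; adding both as covariates gives a small gain in precision at almost no cost.

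*Protocol article*

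**What the plan says.** - **Allocation (Randomisation).** The sequence "will be generated automatically by an online computer program and cannot be influenced by researchers". On stratification: "No stratification procedure is included since the expected number of participants is sufficient to make a balanced distribution among the two parallel groups likely".
- **Timing (Randomisation).** "Randomisation will take place after completion of the screening procedure, informed consent statement and baseline questionnaires". Those questionnaires cover "socio-demographic characteristics, such as age, gender, educational/vocational information" (Assessment).
- **Balance check (Randomisation).** "Randomisation checks will be conducted on baseline behavioural and psychological measures using multivariate analyses of variance (MANOVA"). The outcomes of this check are substance use and the related cognitions, and arm is its sole factor.
- **Main model (Statistical analyses).** For alcohol: "multivariate analyses of covariance (MANCOVA) with intervention condition as the independent variable (intervention vs. control group"). The covariates are the baseline values of the outcomes and change scores in implementation intentions and the Theory of Planned Behaviour constructs. The drug outcomes are handled analogously. Neither country nor sex is listed.
- **Moderators (Statistical analyses).** Sex and "country of residence (Sweden, Germany, Belgium, Czech Republic") appear in a further list of variables to be tested as moderators.
- **Numbers (Sample size).** The aim is 200 per country, 800 in total and 400 per condition, with 50% loss as the worst case.

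**The concern.** The protocol itself treats country and sex as related to drinking:

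- The binge threshold is five drinks, but four for girls (Primary outcomes).
- The typical-quantity item is replaced by a graphical one because standard drinks differ between countries (Primary outcomes).
- Weekly intake is compared with national limits, and the German example differs by sex (Primary outcomes).
- A previous web-based trial in young binge drinkers is reported as showing larger effects in males (Screening and brief interventions).
- International comparison is claimed as a strength (Discussion).

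The main treatment contrast nevertheless uses neither variable. Any country or sex difference in follow-up consumption that baseline consumption does not carry stays in the error term. Any chance difference between arms in country or sex mix goes uncorrected. The planned check would not reveal such a difference, because its dependent variables are consumption and cognitions, and the article attaches no action to its result.

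At stake is some precision in the primary comparison and some tidiness in the country comparisons.

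**Working it through.** **1. The protocol's own balance claim.** With 800 participants and simple 1:1 allocation (binomial, p = 0.5), the 95% range for one arm is 372 to 428. The claim of likely overall balance is correct.

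**2. Balance within a country.** The inputs are 200 randomised per country and, after 50% loss, 100 completers. For four independent countries, P(at least one) = 1 − (1 − p)^4. Efficiency relative to equal arms is 4q(1 − q), where q is one arm's share, and the standard error is multiplied by 1/√efficiency.

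| Setting | Split or worse | p, one country | P, at least one of four | Efficiency at that split | Standard error |
|---|---|---|---|---|---|
| 200 randomised | 90:110 | 0.179 | 0.55 | 4 × 0.45 × 0.55 = 0.99 | +0.5% |
| 100 completers | 40:60 | 0.057 | 0.21 | 4 × 0.40 × 0.60 = 0.96 | +2% |

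Uneven splits are fairly likely, but they cost little. For d = 0.2 in one country with 100 completers, one-sided power is 0.260 at 50:50 and 0.253 at 40:60.

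**3. Validity and the contribution of each change.** The material is a simulation of 400 completers, 100 per country, with 6,000 runs per cell. The outcome has no baseline covariate, and country and sex together explain a share R² of its variance. Without stratification or adjustment, one-sided type I error was 0.052, 0.050 and 0.044 at R² = 0.02, 0.10 and 0.20, against a nominal 0.05. Power at R² = 0.10 and d = 0.2 was:

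| | No country or sex terms | With both terms |
|---|---|---|
| Simple allocation | 0.636 | 0.674 |
| Stratified by country | 0.645 | 0.676 |

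The terms do nearly all the work. Once they are in the model, stratifying moves power from 0.674 to 0.676.

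**4. Gain in a model that already adjusts for baseline.** From Sample size: d = 0.2, one-sided α = 0.05, and 400 per arm less 50%, which is 200 per arm. Two inputs are assumed, because the document gives neither: a baseline-follow-up correlation r = 0.5, and a share f of the variance left after baseline adjustment that country and sex explain.

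SE = √[(1 − r²)(1 − f) × 2/200], and power = Φ(0.2/SE − 1.645).

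| r | f | SE | 0.2/SE | Power |
|---|---|---|---|---|
| 0.5 | 0 | 0.0866 | 2.309 | 0.747 |
| 0.5 | 0.02 | 0.0857 | 2.333 | 0.754 |
| 0.5 | 0.05 | 0.0844 | 2.369 | 0.766 |
| 0.5 | 0.10 | 0.0822 | 2.434 | 0.785 |

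Effective sample size is multiplied by 1/(1 − f), which is 1.02 at f = 0.02 and 1.11 at f = 0.10. With no baseline adjustment (r = 0), the same formula gives 0.639 at f = 0, and 0.646 to 0.678 over the same range of f. Those figures do not describe the planned model, which does adjust for baseline.

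**5. Cost.** Country takes 3 degrees of freedom and sex 1. Of the 400 − 2 = 398 residual degrees of freedom before any covariate, 4/398 is about 1%.

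**The case against.** The strongest reply is that nothing here is misstated. The sentence on stratification speaks only of balance between the two arms, and that is likely at 800. Simple randomisation is valid, country and sex are both examined as moderators, and baseline drinking should already carry most stable national and sex differences. All of this stands. It limits the point to precision and places the likely gain towards the lower end of the range shown.

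Four stronger readings are tempting, and the document supports none of them:

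- **That lack of stratification biases the treatment effect.** It does not. Simulated type I error stays close to 0.05.
- **That a 55% or 21% chance of an uneven country undermines the country comparisons.** The splits concerned raise that country's standard error by about 0.5% and 2%.
- **That recruitment is by fixed country quota.** The article states an aim of 200 per country, not a cap.
- **That the terms would repair the trial's power.** Under the assumptions above, power stays below 0.80. Whether 800 is enough is a separate sample-size question. So is the use of post-randomisation change scores as covariates, which this point does not address.

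One practical caveat applies. The Assessment section names gender but not country in its open list of baseline items, and the site also offers an English version, so language does not identify country. Country must be recorded for the moderator test in any case.

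**Conclusion.** The point holds as a small, inexpensive improvement to the analysis model. The article fixes the covariates of its main MANCOVA and leaves out two baseline variables that it treats elsewhere as relevant to drinking. The consequence is lost precision and unadjusted chance imbalance, not bias. The power gain is at most about 4 percentage points (0.747 to 0.785) and under 1 point at the low end (0.747 to 0.754). These figures assume r = 0.5, f between 0.02 and 0.10, and 200 completers per arm. Unstratified allocation can stand.

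**What to change.** 1. In Statistical analyses, prespecify country (four levels) and sex as fixed covariates, beside the baseline value of the outcome, in every primary and secondary model. This costs 4 degrees of freedom and no extra participants, and it works even if allocation has already begun.
2. State that country of residence is recorded before randomisation.
3. Replace the baseline MANOVA with a descriptive baseline table by arm that includes country and sex. Under valid randomisation a significance test can only flag chance, and it corrects nothing.
4. Optionally, if allocation has not begun, stratify the automated allocation by country with blocks of varying size. This is a small change to the program. It mainly evens out the arms within each country and adds almost no power once step 1 is in place.
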